## Methods

### Participants

Included are patients diagnosed with a psychotic disorder at seven mental health institutions in the Netherlands: a list of study sites can be obtained from the corresponding author. Written informed consent is obtained from each participant.

### Inclusion criteria

To be eligible to participate, patients must meet all of the following criteria:DSM IV diagnosis of a psychotic disorder according to the Mini International Neuropsychiatric Interview (MINI)Avoiding either shops, streets, public transportation or bars/restaurants as assessed by the Safety Behavior Questionnaire (SBQ)A paranoia score (>40) as assessed by the Green et al. Paranoid Thoughts Scale (GPTS)Age 18–65 years

### Exclusion criteria

IQ ≤70. IQ must be established by a valid instrument, such as the Wechsler Adult Intelligence Scale or Wechsler Intelligence Scale for Children. Information on IQ can be found in the status chart of the patient. In case of doubt, the short form of the WAIS III is used to assess IQInsufficient command of the Dutch languageEpilepsy. If no epilepsy is mentioned in the patient status, this is checked with the patient

### Measurement instruments

#### Social participation (primary outcome)

Social participation is measured with the PsyMate experience sampling device. This form of Experience Sampling Measurement (ESM) has high ecological validity [17]. ESM is a self-assessment technique using random time sampling, and has the advantage that it can assess mental state and social context in everyday life as it occurs. Because the ESM assesses ‘at the moment’ it is less vulnerable for recall bias and a valuable instrument to assess clinical phenomena in the real world [18]. ESM is effective for patients with a psychotic disorder with current symptoms, as well as for patients with a psychotic disorder in remission [19]. A review of studies using the ESM shows it to be valid for measuring situational characteristics, such as social environment [20]. Event stress, social environment and company (time spent in company with others and the kind of company) are operationalized in accordance with the work of Collip et al. [19]. Research on the (social) context of delusions in schizophrenia shows the ESM to be a valid aid in collecting data of daily life social situations [21]. Momentary paranoia, using four established ESM items, is a valid state measure to assess paranoia [22]. Perceived social threat, using four established ESM items, is a valid measure to assess perceived social threat as a more subtle indicator of paranoia [19]. An overview of measurement objectives can be found in Table1.

### Eligibility measurements

#### Psychotic disorders

The MINI-Plus interview is used for diagnosing lifetime psychotic disorders. This interview provides a reliable DSM diagnosis for psychotic disorders. The good psychometric characteristics of the MINI (-Plus) make it a good choice for research purposes [23–25].

### Paranoid thoughts

Paranoia symptoms are assessed with the GPTS [26]. The GPTS consists of 32 items divided into two 16-item scales, assessing ideas of social reference and persecution. Good internal consistency and validity are established for both of the scales and their dimensions [26].

### Safety behavior

The Safety Behavior Questionnaire – persecutory delusions (SBQ) is used to assess safety behaviors (such as avoidance) for social situations [27]. An action was considered to be safety behavior if the patient reported that it had been carried out with the aim to reduce a persecutory threat. The patient was asked to rate the frequency of the safety behavior over the last month on a 4-point scale. Psychometric properties of the SBQ range from poor to excellent [27].

### Secondary outcome measures

#### Quality of life

The Manchester Short Assessment of quality of life (MANSA) is a brief instrument used to assess quality of life, focusing on satisfaction with life as a whole and with life domains. Its psychometric properties are satisfactory [28].

### Interaction anxiety

Interaction anxiety symptoms were assessed with the Social Interaction Anxiety Scale (SIAS) [29]. The SIAS consists of 19 items that assess the tendency to fear and avoid social situations. Responses can range from 0 (not at all) to 4 (extremely). The SIAS has good psychometric properties [29, 30].

### Social functioning

The Social and Occupational Functioning Assessment Scale (SOFAS) is used to subjectively assess and rate social and occupational functioning, but not psychological symptoms [31, 32].

### Depression

The Beck Depression Inventory-II (BDI-II) consists of 21 items assessing symptoms and level of depression over the past 2 weeks. The BDI-II is a psychometrically sound instrument [33].

### Moderators and mediators

#### Stigma

The Internalized Stigma of Mental Illness (ISMI) is a 29-item questionnaire that measures self-stigma among persons with psychiatric disorders. The ISMI shows reliability and validity [34].

### Schemata

Schemata of self and others (Brief Core Schema Scales; BCSS) have 24 items concerning beliefs about the self and others that are assessed on a 5-point rating scale (0–4). The BCSS has good psychometric properties [35].

### Cognitive biases

The Davos Assessment of Cognitive Biases Scale (DACOBS) has seven independent subscales each with six items; jumping to conclusions, belief inflexibility bias, attention for threat bias, external attribution bias, social cognition problems, subjective cognitive problems and safety behavior. The DACOBS is reliable and valid for use in clinical practice and research [36].

### Medication adherence

The Brief Adherence Rating Scale (BARS) is an instrument used to assess the antipsychotic medication adherence of patients with a psychotic disorder. The BARS consists of four items: three questions and an overall visual analog rating scale to assess the proportion of doses taken by the patient in the past month (0–100 %). The psychometric properties are adequate [37].

Participants and their psychiatrists are asked not to change any medication during the trial.

### Simulator sickness

The Simulator Sickness Questionnaire (SSQ) was developed to accommodate symptoms specific to simulator technology. The SSQ requires the user to report the subjective severity of symptoms such as general discomfort, headache, eyestrain and fatigue [15]. Although its psychometric properties are adequate, there is room for improvement [38].

### Presence

The Igroup Presence Questionnaire (IPQ) consists of 14 items assessing sense of presence in virtual environments. Responses are made on a 7-point Likert scale. The IPQ has demonstrated good psychometric properties [39].

### Cost-effectiveness

The Trimbos/iMTA questionnaire for Costs associated with Psychiatric illness (the TiC-P) is designed for self-report by patients with a mental disorder. The questionnaire focuses on establishing direct medical costs and productivity costs during paid or unpaid work. The psychometric properties are reported to be adequate [40].

## Design

The study is a single blind randomized controlled trial (RCT) with two conditions: (i) the active condition in which subjects receive the VR treatment besides treatments as usual (TAU) and (ii) the waiting list condition during which subjects receive TAU only. All participants on the waiting list are also offered the VR treatment after follow-up measurements have been completed. The two groups are compared at baseline, at 3 months posttreatment and at 6 months follow-up. The waiting list condition receives the VRET treatment after 6 months.

### Power and sample size calculation

In this RCT, the effect of VRETp on social participation is investigated by comparing this treatment with a waiting list condition. Social participation is assessed with the PsyMate experience sampling method (ESM; see “Measurements”). Self-assessments are rated on a 7-point Likert scale. Main outcome items are social environment and company, perceived social threat in company, event stress, and momentary paranoia. Estimated mean scores and standard deviations (SD) are not readily available because there are no previous VRETp studies with psychotic patients.

Using an estimated (moderate) effect size of 0.5 with a power of 0.8, an alpha of 0.05 and a two-sided independent *t* test, yields *n* = 64 in each group. Therefore, at least 64 participants need to be included in each arm (total *n* = 128 patients). As attrition is estimated at about 20 %, 80 participants need to be included in each condition (total *n* = 160 patients).

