### Objectives

As this is a new form of treatment for social withdrawal in psychosis, the first step is to demonstrate the effect of VRET compared to a waiting list condition on social participation in real life. Objective social participation is defined as the time spent in social situations with other people and the time spent interacting with other people in everyday life. Subjective social participation is how patients experience these social situations; this experience is expressed as momentary paranoia, perceived social threat and event stress, as experienced in situations with other people.

We hypothesize that, after applying the intervention for patients with paranoia (VRETp), they will show improved social participation.

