### Primary objective

To determine the effectiveness of VRETp in patients with psychosis, defined as improved social participation.

Hypothesis 1: The amount of time spent with other people will increase, as measured 60 times a week in real life.

Hypothesis 2: Momentary paranoia, perceived social threat and event stress as experienced in social situations will decline, as measured 60 times a week in real life.

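### The sample size is right for one t test, but the primary outcome is four equal measures and the protocol does not say which measure or time point that test concerns

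*Protocol article*

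**What the plan says.** All references are to the protocol article.

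- **Abstract, Methods/design:** the primary outcome is given in the singular, as social participation.
- **Primary objective:** Hypothesis 1 is that time spent with other people will increase. Hypothesis 2 is that "Momentary paranoia, perceived social threat and event stress as experienced in social situations will decline". Together they cover four measures under one objective.
- **Power and sample size calculation:** "Main outcome items are social environment and company, perceived social threat in company, event stress, and momentary paranoia". The list is unranked. The calculation that follows uses one test: "effect size of 0.5 with a power of 0.8, an alpha of 0.05 and a two-sided independent" t test. The effect size is not tied to any item on the list.
- **Objectives:** objective participation is defined as "the time spent in social situations with other people and the time spent interacting with other people". Hypothesis 1 takes up only the first of these two times.
- **Design:** "The two groups are compared at baseline, at 3 months posttreatment and at 6 months follow-up". Table 1 schedules the experience sampling measure at both T3 and T6.
- **Data analysis:** a multilevel mixed model by intention to treat. No composite, joint test, order of testing or division of alpha is mentioned.

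**The concern.** Alpha and power belong to a decision rule. The article gives both for a single test, but its primary claim, improved social participation, rests on a set of measures listed as equals. A reader of the results could not tell in advance which finding would confirm the primary objective.

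Two things are at stake. If a favourable result on any one measure were taken as success, the chance of a false positive would exceed 5%. If all measures had to succeed, or alpha were divided among them, the chance of success would be below 80%. The answer also matters further on: the abstract makes the cost-effectiveness analysis conditional on effectiveness, and the Data analysis section uses social participation as its outcome, so both need one definition of it.

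**Working it through.** **Inputs from the protocol.** Standardised effect d = 0.5, two-sided alpha 0.05, power 0.8, attrition 20% (Power and sample size calculation); equal allocation (Randomization); four measures (Primary objective; Power and sample size calculation).

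**Inputs assumed.** The protocol gives no correlations between measures and no effect per measure. I take d = 0.5 on every measure and a common correlation r between the test statistics, from 0 to 0.9.

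**Step 1. Reproduce the plan's figure.**
- Normal approximation: n = 2(1.960 + 0.842)² / 0.5² = 62.8, so 63 per arm.
- Noncentral t: n = 63.77, so 64 per arm, with power 0.801.
- Attrition: 64 / (1 − 0.2) = 80 per arm, 160 in total.

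The stated figures are reproduced.

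**Step 2. Four measures at posttreatment, 64 per arm.** The expected test statistic under d = 0.5 is 0.5 / √(2/64) = 2.83. Where r > 0, the results come from 1,000,000 draws of four equally correlated normal statistics.

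| Rule | r = 0 | r = 0.5 | r = 0.9 |
|---|---|---|---|
| Any one suffices, each at 0.05: false-positive rate | 18.5% | 15.5% | 9.4% |
| All four must succeed, each at 0.05: power | 43% | 57% | 71% |

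Checks at r = 0: 1 − 0.95⁴ = 0.185 for the error. For power, the exact t gives 0.8015⁴ = 0.413; the 43% comes from the normal approximation.

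**Step 3. Alpha divided or stepped over four measures.**
- Bonferroni: 0.05 / 4 = 0.0125, and noncentral t power per test is 0.616.
- Holm: average power per test is about 74% (r = 0), 72% (r = 0.5) and 70% (r = 0.9). Holm never rejects less often than Bonferroni, so 62% is its floor. The chance of at least one Holm success is about 98%, 89% and 75%.

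**Step 4. Upper bound on the count.** Adding T6 gives 4 × 2 = 8 tests; adding time interacting as well gives 5 × 2 = 10. For r = 0 to 0.9, the any-one error is 34% to 12% for 8 tests and 40% to 13% for 10. Bonferroni power per test is 52% and 49%.

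**The case against.** The strongest reply is that this is mostly an absence. An article condenses the full protocol, and a multiplicity method may stand in an analysis plan that is not shown. That is fair, and a missing multiplicity method alone would be no finding. What remains is in the printed text: a list of equal main outcome items beside a single-test calculation that names none of them.

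Four stronger readings might be inferred, and the document does not support them.

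- **That the sample size is wrong.** It is not. Both 64 and 80 per arm follow from the stated inputs.
- **That the plan accepts any one significant measure as success.** No section says so, and Hypothesis 2 joins its three measures with "and". If all must succeed, the error is not inflated and the problem is power alone. If any one suffices, power exceeds 80% (about 89% to 99.9% for four measures) and the problem is error alone. The two failures belong to different rules and do not occur together.
- **That there are eight to ten primary tests.** Time interacting is in the definition under Objectives but not in Hypothesis 1. The abstract's Discussion presents posttreatment results as the main evidence of effectiveness and the 6-month data as evidence on long-term effects. This does not formally designate a primary time point, but it makes eight to ten an upper bound.
- **That the error is several times 5% whatever the correlation.** The section on social participation describes perceived social threat as a subtler indicator of paranoia, so independence between those two is implausible. At r = 0.9 the error is 9.4%, roughly double the nominal level.

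**Conclusion.** The point holds in a limited form. The calculation is correct for one test, but the protocol does not identify that test, and its primary outcome is four measures of equal standing. While they stand as equals with no combined test, at least one of the two stated figures does not describe the primary claim: the error is about 19% to 9% if any one suffices, or power is about 43% to 71% if all must succeed, or 62% per test under Bonferroni.

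These sizes count posttreatment only and rest on an assumed d = 0.5 for every measure and an assumed correlation of 0 to 0.9. The direction is the same throughout that range. Both stated figures can stand once a single deciding test is named.

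**What to change.** Name one measure at one time point as the deciding test, two-sided at 0.05. Time in company at T3 is a natural example, being the first-listed hypothesis at the time the abstract emphasises. Nothing in the protocol ranks the measures, however, and the sponsor may choose another to lead. Test the other three primary measures behind it in a stated fixed order, treat T6 as secondary, and say whether time interacting is part of the primary outcome. State that the 80% power applies to the first test only. Under the same d = 0.5, the chance that the first two both succeed would be 0.8015² = 64% if independent, and higher with positive correlation.

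If all four are to remain co-primary, state a Holm rule and give the power as about 70% to 74% on average per test, with 62% as the floor. Restoring 80% per test under Bonferroni would need 91 per arm, or 91 / 0.8 = 113.75, so 114 per arm after attrition (228 in total against the planned 160).

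The preferred change affects wording in the objectives, sample size and analysis sections only. It needs no extra patients or data. The downside is that fewer measures carry an unconditional primary claim.

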### Procedure

Patients with a chart diagnosis of schizophrenia, schizophreniform disorder, schizoaffective disorder, delusional disorder or psychotic disorder not otherwise specified (NOS), will be informed about the study by their treating specialist and asked to participate. Each patient is asked for written permission to be contacted by the researchers if eligible for VRETp. If eligible, the treating specialist discusses participation of the patient in the study with the remainder of the team and gives permission to the researchers to contact the patient. When permission is given, additional information is provided and patients have 2 weeks to consider whether they really wish to participate. The VRETp treatment is additional to current treatment and declining to participate has no negative consequences at all for patients. For each of the participating organizations an independent specialist is available for patients to contact. Contact information of this specialist is available in the information letter given to the patients of the participating organizations.

Informed consent from all participants is obtained before assessment by the researcher. The MINI-Plus interview is used to diagnose psychotic disorders. Patients who are willing to participate are screened for avoidance behavior (SBQ) and for paranoia using the GPTS (cutoff >40) of Green et al. Baseline measurements are obtained. Randomization is used to allocate a patient to either the VRETP or to the waiting list condition. Patients allocated to the VRETp group start their treatment, which consists of a maximum of 16 sessions with a maximum duration of 60 minutes each.

At baseline (T0) the research assistant assesses the baseline measurement of all primary and secondary variables. At 2 weeks (T1) and 4 weeks (T2) into treatment, respectively, participants in the treatment condition are assessed for their scores on paranoia, interaction anxiety, cyber sickness, presence in the virtual world and medication adherence, using self-report questionnaires handed out by the therapist, or interview questions (medication adherence).

At the end of treatment (T3) and at follow-up (T6), the research assistant assesses the primary and secondary measures.

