### Side effects and safety

A phenomenon called simulator sickness (also known as cyber sickness) can occur when using VR applications. Symptoms are similar to those of motion-induced sickness, but tend to be less severe and have a lower incidence [15]. It is suggested that simulator sickness sensations can be at least partially explained by an overlap with anxiety symptoms [16]. A pilot study on virtual reality and psychosis showed low symptoms of simulator sickness, and no significant increase between pre- and post-measurement [11]. Since simulator sickness is known to increase with the duration of exposure [15], measurement of these symptoms will be included in the study protocol.

No adverse effects were found in studies using VR to expose psychotic patients to virtual social environments. A study with 20 psychotic patients diagnosed with first-episode psychosis experiencing at least moderate paranoia found that VR did not lead to more anxiety or physical complaints directly after the experiments; follow-up 1 week later showed that no patients reported an increase in intrusive negative thoughts, unpleasant emotions or behavioral changes as a consequence of the VR experience [16]. Similar results were found in a study of 21 patients with at-risk mental state for psychosis [8]. Our own pilot study confirmed that patients did not become more psychotic as a result of exposure to our virtual social environment [11].

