### Virtual reality exposure therapy (VRET)

VRETp treatment has a maximum of 16 treatment sessions of 60 minutes each. This number of sessions is somewhat larger than is usual for CBT in anxiety disorders. Our rationale for this is our expectation that treating paranoia requires more time compared with treating regular anxiety. People suffering from a psychotic disorder often show severity and durance in their social avoidance. Negative symptoms make it difficult to motivate people for therapy and this is a continuing process during treatment. The treatment protocol states that the therapists receive 16 hours of training; all therapy sessions are recorded. A selection of the sessions is rated for treatment fidelity using the Cognitive Therapy Rating Scale (CTRS). The CTRS is a reliable [41] and valid [42] instrument to measure treatment fidelity when following a CBT protocol. Monthly 4-hour group supervision serves to guide the therapists throughout the intervention period.

Existing CBT protocols will be adapted for VRET treatment in one area: exposure in vivo will be replaced by VR exposure. The remainder of the treatment protocol consists of well-known, evidence-based CBT elements, e.g., providing treatment rationale, behavioral experiments, reducing safety behavior, and attention training. Starting with exposure exercises for social situations, which are lowest in the patient’s anxiety hierarchy, the exposure exercises take place during the therapy session using the Virtual Reality system. Participants are not allowed to receive any other form of therapy aimed at improving social participation during the trial. At all times the therapist is in control of the VRETp intervention and is able to immediately change/stop the virtual environment if necessary.

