### Discontinuation

Participation is completely voluntary and participants can withdraw from participation at any time for any reason. Participants who drop out or otherwise deviate from the intervention protocol are requested to continue to participate in the measurements.

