### Adverse events

The rules and regulations of the Medical Ethics Committee concerning adverse events are followed. All participants are insured in case any harm is caused related to trial participation.

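### The simulator sickness and presence forms are first given at session 4, so a VRETp patient who stops VR before then has no score, and reported sickness would be too low if sickness caused some of those stops

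*Protocol article*

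**What the plan says.** All references are to the protocol article.

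- **Side effects and safety** gives the reason for measuring simulator sickness: "Since simulator sickness is known to increase with the duration of exposure", so "measurement of these symptoms will be included in the study protocol".
- **Table 1** has crosses for the SSQ and the IPQ under T1 (session 4) and T2 (session 8) only. There is none at baseline, T3 (posttreatment) or T6 (follow-up).
- **Procedure** confines T1 and T2 to the VRETp arm: "At 2 weeks (T1) and 4 weeks (T2) into treatment, respectively, participants in the treatment condition are assessed for their scores on paranoia", together with interaction anxiety, cyber sickness, presence and medication adherence. The self-report forms come from the therapist: "using self-report questionnaires handed out by the therapist".
- **Virtual reality exposure therapy (VRET)** sets the length of the course: "VRETp treatment has a maximum of 16 treatment sessions of 60 minutes each".
- **Discontinuation** covers patients who stop: "Participants who drop out or otherwise deviate from the intervention protocol are requested to continue to participate in the measurements".
- **Adverse events** gives a general rule: "The rules and regulations of the Medical Ethics Committee concerning adverse events are followed".
- **Secondary objectives** lists simulator sickness and presence among the moderators and mediators. Acceptability is a separate item in the same list.

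**The concern.** Simulator sickness is the one VR side effect for which the article plans a questionnaire. Its first measurement comes after three complete sessions. A patient made ill in sessions 1 to 3, and who stops for that reason, is missing from the sickness data because of the symptom being measured. An average or rate taken at session 4 or 8 then describes the patients who stayed long enough to be asked.

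Two uses of the data are exposed. The first is the description of how well VR was tolerated. The second is the moderator and mediator analysis, which would lack these patients for both variables. The schedule itself creates the gap, so a later analysis plan cannot fill it: a score that was never collected cannot be recovered.

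**Working it through.** **1. The plan's own figure.** The article computes only a sample size. Inputs from Power and sample size calculation: effect size 0.5, power 0.8, two-sided alpha 0.05.

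- Normal approximation: n = 2 × (1.960 + 0.842)² / 0.5² = 62.8, so 63 per arm.
- t test: 63.77, so 64 per arm, as stated.
- With 20% attrition: 64 / (1 − 0.20) = 80 per arm, as stated.

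These figures are not in dispute. They imply 80 × 0.20 = 16 expected losses in the VRETp arm. The article does not divide them by arm, by cause, by session, or between leaving treatment and leaving the study.

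**2. Which scores each patient has.** Reading Table 1 with Procedure:

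| VR stopped | Session 4 form | Session 8 form | T3, T6 | SSQ/IPQ scores |
|---|---|---|---|---|
| before session 4 | no | no | not scheduled | 0 |
| from session 4, before session 8 | yes | no | not scheduled | 1 |
| at or after session 8 | yes | yes | not scheduled | 2 |

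Only the first row leaves a patient with no score. Staying in the study does not change that row, because the later visits contain neither form.

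**3. How many patients could be in the first row (assumption).** Suppose all 16 losses were stops of treatment.

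- Spread evenly over 16 sessions by last session attended, that is one per session. Sessions 1, 2 and 3 give 3 of 80 (3.75%).
- If half fell before session 4: 8 of 80 (10%).

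**4. When the rate falls below the truth.** Let N patients have VR and K of them have marked sickness. Let m go unscored, of whom k were sick. Then

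observed rate = (K − k) / (N − m), true rate = K / N.

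The observed rate is below the true one only if k/m > K/N, that is, if sickness is commoner among the unscored patients than overall.

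Illustration with N = 80 and an assumed K = 12 (15%):

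| m | k | Observed |
|---|---|---|
| 8 | 1 | 11/72 = 15.3% |
| 8 | 4 | 8/72 = 11.1% |
| 8 | 8 | 4/72 = 5.6% |
| 4 | 1 | 11/76 = 14.5% |

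With m = 8 the break-even is 8 × 0.15 = 1.2 sick patients. One sick leaver therefore gives no shortfall, and the last case, where all eight were sick, is an extreme.

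**5. The same in rates.** Let p be the rate among scored patients, d the unscored share of the arm, and s the share of the unscored who stopped because of sickness. The other unscored patients are taken to have rate p. Then

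true rate = (1 − d)p + d[s + (1 − s)p], so shortfall = d × s × (1 − p).

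With an assumed p = 10%:

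- s = 0: no shortfall.
- d = 5%, s = 25%: 0.05 × 0.25 × 0.9 = 1.1 points.
- d = 10%, s = 25%: 2.25 points.
- d = 20%, s = 50%: 9.0 points. Here the whole 20% attrition would have to fall before session 4, so this is the far end.

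None of p, d, s or K is given in the article.

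**The case against.** **The drop-out rule could cover it.** Procedure refers to participants in the treatment condition, not to those still attending, and Discontinuation excludes no visit. Procedure also times T1 and T2 by weeks. A patient who had stopped could, on that reading, still be given the form at week 2. This is fair as far as the wording goes. But the article gives no route by which a form handed out by the therapist reaches someone who no longer attends, and a form completed without a recent VR session would not record how VR was tolerated. The gap remains.

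**The effect is probably small.** The Side effects and safety section reports low sickness in the pilot study, with no significant rise. It also reports no increase in physical complaints among 20 first-episode patients. This stands, and is why no size is claimed.

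**Stronger readings a reader might infer.**

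- That every early stopper goes unscored. Table 1 shows otherwise: a patient who stops between sessions 4 and 8 has one score, and a later stopper has both.
- That reported sickness is biased low as a matter of fact. This depends on sickness-driven stops before session 4, on which the article gives no figure.
- That the acceptability objective is distorted. Nothing in the article says acceptability is measured by the SSQ or IPQ.
- That presence scores are biased in a known direction. The article supports only that these patients' scores are missing.

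**Some of this belongs in the full protocol.** Recording reasons for stopping and the detail of adverse event reporting are matters an article may leave out. The therapist's report on each session, described under Fidelity checks, or the adverse event route may capture a stop caused by sickness. It cannot be assumed that such stops are lost. That part of the objection stands. It does not reach the schedule in Table 1, which the article states in full.

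**Conclusion.** The point holds in a limited form. The stated schedule leaves a VRETp patient who stops VR before session 4 without a simulator sickness or presence score, and no later visit supplies one. If sickness is commoner among those patients than in the rest of the arm, the reported rate will be too low. The moderator and mediator analyses lack these patients in any case.

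The size cannot be derived from the document. Under the assumed inputs above the shortfall runs from nothing to 9 percentage points. The upper end needs both the full 20% attrition before session 4 and half of it caused by sickness. The even spread (3 of 80 unscored) leaves room for much less.

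The comparison of arms on social participation does not use these forms and is unaffected. This is a cheap improvement to tolerability data, not a threat to the trial's main result.

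**What to change.** In Table 1 and in Procedure, add the SSQ and IPQ at the end of the first VR session, and keep sessions 4 and 8. Each patient exposed to VR then has at least one scheduled score.

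Report sickness with all patients who had at least one VR session as the denominator. Count a known stop for simulator sickness as a sickness event, whether or not a form was completed. This covers patients whose symptoms developed after the first session and before session 4, where the reason is known.

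A form at the last session attended is not proposed, because it cannot be scheduled for a patient who simply stops coming.

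The cost is a few minutes per patient on forms already in use, and a sickness rate that may look less favourable. The article gives the trial status as ongoing, so the extra form could be introduced only for patients yet to start VR. The denominator and the counting of known stops can be applied to everyone, with the number lacking any form stated.
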